### Sensitivity and subgroup analyses

Our primary analysis will be an intention to treat analysis. However, to account for any contamination between the standard care and intervention arms, we will carry out a per-protocol analysis.

Where available, we will also measure the difference in vaccine uptake, comparing practices that used the exact wording of the message in the study protocol with practices that used an alternative message. We hypothesise that practices using our message (based on behavioural theory) will have a higher uptake than an alternative designed by the practice. As this will be a non-randomised comparison, we will adjust for confounders.

Finally, we will compare the effectiveness of the text message based on the time of day that it was sent to patients. We hypothesise that messages sent in the late afternoon will have more effect than those sent at earlier times of the day, when patients may not have the time to respond.

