### Assignment of interventions

Practices will be randomised on a 1:1 basis to the intervention and standard care groups. We will use block randomisation within each setting. In the CPRD and ResearchOne, we will stratify by region. The allocation sequence will be generated by an independent statistician who will be blinded to practice name and the allocation sequence will be concealed from the study team. Once practices have been allocated, the trial coordinator will inform practices about their allocation and distribute study materials.

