### Interventions

Practices will be allocated to an intervention or standard care arm. Those in the intervention arm will be asked to send an influenza vaccination text message reminder to their under 65 at-risk patients. This includes patients who are under 65 with chronic heart disease, chronic neurological disease, diabetes, chronic kidney disease, chronic liver disease, chronic respiratory disease and immunosuppression, as set out by the Chief Medical Officer.^17^ Most practices will identify eligible patients based on their electronic medical records using their established systems. Practices use a standard set of Read codes (available from Primis^18^) to determine patient eligibility for influenza vaccination.

The message content that practices will be asked to send is shown in box 1. This single text message was designed to be a pragmatic, uncomplicated intervention that would not discourage practices from participating, but that aims to address some of the key barriers to vaccination.^3^ It was specifically designed to target more than one factor influencing behaviour: first, the text message represents a recommendation from the general practitioner (GP); second, it indicates the severity of flu and that the patient is susceptible to flu; third, it acts as a prompt to patients who might have simply forgotten to make an appointment.
Box 1 Recommended text message content in the trial intervention arm.Hello *PATIENT NAME*, to reduce your risk of serious health problems from flu, we recommend vaccination. Call *PRACTICE PHONE NUMBER* to book. *PRACTICE NAME.*

Practices in the intervention group will receive guidance notes regarding delivery of the message (content, timing, eligible patients) and an incentive payment of £200. Practices will be instructed to continue with any other aspect of their seasonal flu campaign as planned, in addition to the text message. An online questionnaire will be sent to practices in the intervention arm to ascertain feedback from practice staff about delivery of the intervention.

Practices allocated to the standard care group will be asked to continue with their seasonal flu campaign as planned.

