## Statistical methods

A cluster-level analysis will be performed using practice-specific proportions as observations. We will compare vaccine uptake in the intervention and standard care groups using a t test, with the size of clusters taken into account. A series of descriptive statistics will describe the methodological outcomes.

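### The time-of-day comparison is as non-randomised as the message-wording comparison, but confounder adjustment is stated only for wording

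*Protocol article*

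**What the plan says.** All references are to the protocol article.

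- **Assignment of interventions:** "Practices will be randomised on a 1:1 basis to the intervention and standard care groups". Nothing else is randomised; no section assigns a sending time.
- **Interventions:** the practices send the message themselves and receive "guidance notes regarding delivery of the message (content, timing, eligible patients". What the notes say about timing is not shown.
- **Sensitivity and subgroup analyses, wording:** practices that used the protocol's exact message are compared with practices that used another one, and the article adds: "As this will be a non-randomised comparison, we will adjust for confounders".
- **Same section, next paragraph, time of day:** "we will compare the effectiveness of the text message based on the time of day that it was sent to patients". A direction is given: "We hypothesise that messages sent in the late afternoon will have more effect than those sent at earlier times of the day". No adjustment is stated, and the comparison is not called non-randomised.
- **Statistical methods:** "A cluster-level analysis will be performed using practice-specific proportions as observations". The only test named is a t test between the two randomised arms, allowing for cluster size.
- **Outcomes and Data collection methods:** the primary outcome is vaccination by 31 December 2013, and uptake is analysed from 1 September to that date. No other period is given for any comparison.

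**The concern.** Time of day, like wording, is a feature of how an intervention practice carried out the campaign after allocation. Practices that send in the late afternoon may differ from the others in organisation, staffing, patient mix or the date in the season on which they sent. Software may matter too: under Inclusion criteria, CPRD and London practices use iPLATO and ResearchOne practices use SystmOne, so sending time could follow setting. Standard care practices have no assigned sending time, so the randomised comparator cannot repair the contrast.

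The article gives the right reason for adjusting the wording comparison and then does not carry it to the next paragraph, where the reason holds equally. Followed as written, a difference between practices could be taken as confirming the timing hypothesis.

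The outcome period adds a second difficulty. A vaccination given before the message was sent cannot be a response to its time of day. Counting such vaccinations does no harm in the intention-to-treat comparison of arms. In a comparison by sending time it mixes in uptake that the message could not have caused, and unevenly so if sending dates differ between the groups.

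**Working it through.** **Text, side by side**

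| | Wording | Time of day |
|---|---|---|
| Randomised? | No | No |
| Who carries it out | The practice | The practice, with guidance on timing |
| Directional hypothesis | Yes | Yes |
| Called non-randomised | Yes | No |
| Adjustment stated | Yes | No |

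The two rows that justify adjustment (not randomised, carried out by the practice) agree. The two that record the consequence differ.

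**Illustration of size.** The plan gives no figure for this comparison, so there is none to reproduce. The inputs come from the Sample size calculation section: ICC 0.024, 750 eligible patients per practice, uptake 54% and 58%, and 150 practices randomised 1:1, hence about 75 in the intervention arm. Assumptions not in the documents: each practice sends at one time of day, the split is even (37.5 and 37.5), and a normal approximation is used at two-sided 5%.

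1. Between-practice SD = √(0.024 × 0.54 × 0.46) = √0.00596 = 0.0772, or 7.7 points.
2. SD of observed practice proportions, adding sampling variation at the mid-value of 56%: √(0.00596 + 0.56 × 0.44 / 750) = √0.00629 = 0.0793, or 7.9 points.
3. SE of the unadjusted contrast = 7.93 × √(2 / 37.5) = 1.83 points. The 95% half-width is 1.96 × 1.83 = 3.6 points, against the 4-point effect (54% to 58%) for which the whole trial is powered.
4. Suppose timing has no effect but the two groups of practices differ by *b* points in underlying uptake. The probability of a significant result is Φ(*b*/SE − 1.96) + Φ(−*b*/SE − 1.96). For *b* = 2, *b*/SE = 2 / 1.83 = 1.09, which gives 0.19.

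Range over the assumed *b* and the assumed share of practices sending in late afternoon:

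| Share in late afternoon | SE (points) | *b* = 1 | *b* = 2 | *b* = 3 |
|---|---|---|---|---|
| 50% | 1.8 | 8.5% | 19% | 37% |
| 20% (15 v 60) | 2.3 | 7% | 14% | 26% |

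The SE and half-width measure imprecision, not bias. The false-positive rates show what an assumed bias would do; the documents give no estimate of the bias itself.

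**Outcome period.** The recipients are described as at-risk patients under 65, with no stated restriction to those still unvaccinated on the sending date. Under the 1 September to 31 December period, earlier vaccinations would therefore be included. The documents give no sending dates, so neither the number nor the direction of the effect can be computed.

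**The case against.** The best reply is that the article is silent on adjustment here and does not rule it out. The t test is specified for the comparison of arms, not for this one, and the covariates of an exploratory analysis usually belong in a fuller document. This stands in part: a reader might infer that the investigators decided against adjustment, and the text does not support that. But the article does settle the matter for the adjacent comparison, with a reason that applies to both, so the unevenness is in the text itself and is more than omitted detail.

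Other stronger readings also go too far:

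- **That the contrast lies wholly between practices.** The hypothesis speaks of messages sent at different times, and no section says that each practice sends at one time. Some variation within practices is possible. The illustration depends on assuming there is none.
- **That pre-message vaccinations will be counted as response.** The period from 1 September is a general statement under Data collection methods and is not tied to this comparison. The point holds only if that period, the only one given, is used.
- **That the 3.6-point half-width shows confounding.** It does not, and adjustment is not shown to shrink it.
- **That sending slots should be randomised in this trial.** The outcome period closed on 31 December 2013, before the date of the protocol version cited under Approvals (11/02/2014).

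Finally, this is a subgroup analysis that is not listed among the outcomes, and it cannot alter the primary intention-to-treat result. That stands, and it limits the weight of the point.

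**Conclusion.** The point holds as an inconsistency within one section: two comparisons with the same non-randomised status are planned, and only one carries the label and the adjustment. Read as written, the time-of-day hypothesis would be tested on a contrast open to confounding.

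On the illustrative assumptions, the contrast is imprecise, with a half-width close to the trial's whole target effect, and an underlying difference of 2 points, about a quarter of the between-practice SD, would lift the false-positive rate to between 14% and 19%. Those rates rest on an assumed bias. The textual finding does not depend on them. The weight is modest: the comparison is secondary and the correction is cheap.

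**What to change.** In the time-of-day paragraph:

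1. State that the comparison is non-randomised and exploratory.
2. Adjust it as for the wording comparison, and include setting or region, date of sending and, where available, the practice's 2012/13 uptake.
3. Where sending and vaccination dates are available, count only vaccinations after sending, among patients unvaccinated on the sending date. Otherwise report the comparison descriptively, without a test of the hypothesis.

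Adjustment will not remove unmeasured differences between practices, so the exploratory label is needed in any case.

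The cost is minor analysis work plus use of sending dates and prior-season uptake. Neither is named in the list of extracted items under Data collection methods. A comparison by time of day already needs the sending time, so the date should usually be recorded with it. The sample size section quotes 2012/13 uptake for the CPRD, so prior-season data exist in at least that setting. The primary analysis does not change.

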### Hawthorne effect

The study design allows an evaluation of the generalisability of the study population; practices that take part in the study can be compared with other practices outside of the trial that contribute data to ResearchOne and CPRD. We will test whether participation in the trial changes the behaviour of practices in their use of text messaging (Hawthorne effect).

This study will provide evidence regarding the effectiveness of text messaging reminders for influenza vaccine in patients under 65 with chronic conditions. The methodology here will be applied to future cluster randomised trials of text messaging interventions within electronic heath records.

## Ethics and dissemination

### Ethical issues

#### Approvals

The study protocol (V.2.7, 11/02/2014) has received a favourable opinion from the National Research Ethics Service Committee—Surrey Borders (REC number 13/LO/0872) and has also received assurance from participating Primary Care Trusts/Clinical Commissioning Groups. All minor and major amendments to the protocol will be approved by the REC, and participating general practices will be notified of any protocol amendments relevant to them.

#### Informed consent

This is a cluster trial and informed consent will be obtained by the trial coordinator from GPs, who will act as the guardian of the cluster. A signed and dated informed consent form is required for participation in the trial. The risks and benefits of participation will be explained and GPs are free to decline to participate in the trial. Individual consent will not be sought. This is justified because participating practices already use text messaging to communicate with patients, although not systematically for influenza. Patients within these practices will have the opportunity to opt out of receiving messages if they do not wish to be contacted in this way.

#### Patient confidentiality

All patient-level data accessed in this study will be stripped of personal identifiers.

#### Access to data

The data will be accessed only by authorised persons from the London School of Hygiene and Tropical Medicine and research governance authorities to ensure that the study is being carried out to acceptable standards. All will have a duty of confidentiality and no data will be disclosed outside the research site. All patient-level and practice-level information will be confidential.

#### Burden and risk to practices

Text messaging is widely used in everyday primary care and the only substantive change from non-study is the random allocation of a defined text message regarding influenza vaccine rather than the practice's own seasonal flu campaign. Patients can opt out of receiving text messages from their practices, and as part of this study, we will monitor patient and practice complaints regarding the text message. Patients registered at practices in the intervention arm will receive one text message regarding their flu vaccine to minimise irritation to patients.

Participating practices must spend time identifying eligible patients and sending a text message. We are reducing this burden by (1) asking practices to use established procedures and software to identify eligible patients for vaccination. This is a task that they would perform annually in non-study conditions; (2), we are including only practices that are familiar with the text messaging software, which minimises time spent in familiarisation with the software and sending messages; (3) additional support is available to any practice through a guidance document and/or dedicated support helpline and (4) we are providing an incentive payment (£200) to practices in the intervention group to encourage participation.

Practices may experience increased demand for influenza vaccination appointments or run out of vaccine supplies sooner than expected. The increase in uptake is unlikely to be large and will help the practice to achieve their Quality and Outcomes Framework target for vaccination, for which they receive payment.

#### Benefits for practices

Practices in the intervention arm will receive a £200 incentive to participate. If the text message is effective, then increased uptake will result in additional incentive payment to GPs by the government and will help them reach their Quality and Outcomes Framework targets. The results of this trial will allow practices to make an informed decision about spending of their budget on the seasonal influenza campaign.

### Dissemination plans

The results of this trial will be published according to the guidelines of the CONSORT statement. The results will be published in a peer reviewed medical journal and presented at national conferences. The results will also be distributed to the Primary Care Research Network and to all participating general practices. Authorship for all publications will be based on the criteria defined by the International Committee of Medical Journal Editors.^19^
